### Sample

Based on the average population of each school, a cluster size of 100 will be required per school to detect a minimum detectable effect of 0.484 and a statistical power of 80% at a confidence level α = 0.05 for a two-tailed *t*-test (45). Assuming a participant dropout rate of 11.25% from the *Discover Learning* pilot study conducted in 2017 the final sample size will include 500 participants. The nested study will include all participants who have access to a smartphone with WhatsApp functionality. The study will be reported according to CONSORT guidelines.

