##### Baseline and Endline Survey

The adolescent survey will be administered at baseline and endline to measure changes in social emotional learning and health and well-being outcomes. The survey also seeks to capture changes in gender norms, beliefs and behaviors and positive attitudes toward technology as a learning tool. Measures are included to identify involvement of siblings, parents/caregivers and extended family in the intervention modules and seeks to identify which components of the intervention hold the greatest promise for innovation, scale, and adaptation. The survey questions are adapted from various validated measurement scales and modified to suit the study context and target group. One area of focus for this survey is the testing of a contextually relevant principle of *Utu*, an African philosophy of altruism, kindness, compassion and empathy. A summary of all measures included in the survey are listed in Table 1. The VYA survey will be administered by researchers via a phone call or sent via WhatsApp to participants in the nested study group, and will take 45–60 min to complete.

**Table 1 T1:** Summary of measures to be tested in the *Discover*.

**Primary outcome**	**Validated measurement scale**

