**Social Emotional Mindsets**	
Growth mindset	Yeager Growth Mindset (46)
Purpose	The Dimensions of Identity Development Scale (47)
Goal orientation	The Goal Orientation and Learning Strategies Survey (48)
Curiosity	The Trait State Curiosity Scale (49)
Persistence	The Scale for Measuring Persistence in Children (50)
Utu^1^	Measure Scale for Ubuntu (51); and Compassionate Engagement and Action Scale (52)
Social responsibility and cooperation	Teamwork and Collaboration Assessment for High School Students (53)
Persistence	The Scale for Measuring Persistence in Children (50)
Adverse life experiences	Adverse Childhood Experiences Questionnaire (ACE) (54)

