**Social Emotional Skills**	
Teamwork	Teamwork and Collaboration Assessment for High School Students (53)
Empathy	The Empathy Questionnaire for Children and Adolescents (EmQue-CA) (55)
Gender equity	Gender Attitudes Scale - Choices curriculum (56)
Generosity	The Interpersonal Generosity Scale (57)
Resilience	Child & Youth Resilience Measure-Revised (CYRM-R) (58)
Coping skills	Spirito KIDCOPE checklist (59)

1 *Utu refers to is a traditional African philosophy, defined as communicating, caring, and sharing with humans in harmony with all of creation*.

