### Data Analysis

All quantitative data will be cleaned, coded and analyzed in Stata SE 16.0 (62). Statistical analysis will be conducted according to the Intention-To-Treat principle. Participants who do not complete all intervention modules due to attrition or who have missing data will be examined for inclusion in the final analysis. If <2% of the observations contain missing values on each variable and the pattern of missing values is random, then Listwise Deletion method will be used (63). If missing data is not determined to be missing at random, multiple imputation models will be used for analyzing adolescent data (64). All data will be examined for skewness or data non-normality. Multivariate regression models will be used to assess the effect of the intervention on study outcomes and will control for age, gender, socioeconomic status, school and household characteristics. Statistical significance for all analyses will be set at *p* < 0.05. Psychometric analysis of measures including exploratory and confirmatory factor analysis will be used to establish measure validity. Structural equation modeling (SEM) will be used to test structural paths between latent constructs. Potential mediating and modifying variables will be assessed. SEM models will be assessed for goodness of fit using indices including the root mean square error of approximation (RMSEA) (65), the comparative fit index (CFI) (66), the Tucker Lewis Index (TLI) (67) and the standardized root mean residual (SRMR). All qualitative data will be transcribed and translated verbatim from Swahili to English by trained translators. All participant identifiers will be removed from transcripts. All audio recordings of transcripts will be destroyed after transcription is completed and translation have been verified. Translations will be uploaded to Atlas.ti for analysis (68). A grounded theory approach will be used to identify emergent themes (69). The analytical steps will be conducted by two separate analysts. *Line-by-line coding of* each transcript will be used to identify initial codes that capture implicit meanings, and common relationships and significance between codes. Where appropriate codes will be left *in vivo* to preserve participant language and meaning. Next, *focused codes* will be developed from the most significant and/or frequent initial codes to make analytical sense of the data. *Axial coding* will be used to represent the content of focused codes and to connect relationships between codes, categories and concepts. During the application of focused and axial coding, analysts will meet to discuss and revise codes until consensus is reached. Researchers will write memos to capture connections and to construct analytic notes. Researchers will further hold discussions to help identify emergent themes and connections between themes through an iterative deductive process. Exemplar quotes will be selected to illustrate emergent themes. All transcripts will be stored in an access-controlled server that is located safely within the local implementation partner, HPON's Tanzania office and destroyed after 5 years.

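### Fourteen constructs are headed as primary outcomes and every analysis is tested at 0.05, with no lead outcome, composite, testing order or adjustment stated

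*Protocol article*

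**What the plan says.** All of this is in the protocol article.

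- **Baseline and Endline Survey, Table 1.** The only outcome header is "Primary outcome". No secondary heading follows it. The Social Emotional Mindsets block has nine rows and the Social Emotional Skills block has six.
- **Within Table 1.** Persistence appears twice with the same scale. Social responsibility and cooperation (Mindsets) and Teamwork (Skills) both cite the same instrument, reference 53. Adverse life experiences is listed among the Mindsets, measured by the "Adverse Childhood Experiences Questionnaire (ACE) (54").
- **Data Analysis.** "Multivariate regression models will be used to assess the effect of the intervention on study outcomes", with adjustment for demographic, school and household covariates. Then: "Statistical significance for all analyses will be set at" p < 0.05.
- **Sample.** The calculation gives a minimum detectable effect of 0.484 with "a statistical power of 80% at a confidence level α = 0.05 for a two-tailed" t-test. It does not say which outcome that test concerns.

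**The concern.** The sample size section plans for one test, while Table 1 gives primary status to every construct in the survey. The significance rule then sets the same unadjusted level for each of them. Nothing says which result answers the primary research objective, or how many scales must be significant before the programme is said to work. Followed as written, the plan lets a single significant scale be presented as an effect on a primary outcome. The chance that at least one scale reaches p < 0.05 when the programme changes nothing is then far above the 5% a reader would assume.

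What is at stake is the main conclusion: whether the programme improves social emotional learning and identity development. The article also suggests that its findings could be replicated in other low-resource contexts.

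**Working it through.** **Inputs from the article**
- Per-test level: 0.05, two-sided (Data Analysis; Sample).
- Rows under the primary header: 9 + 6 = 15. Less the repeated Persistence row: 14 distinct constructs.
- Less adverse life experiences: 13. Counting the shared teamwork instrument once as well: 12.
- Planned power 80% for an effect of 0.484 (Sample), taken as stated.

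**Input that is assumed.** The article gives no correlation between scales. I take an equal correlation ρ between the test statistics and show a range.

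**The plan's own figure.** The article states no family-wise error rate. The only error rate it gives is 0.05 per analysis, so there is nothing to reproduce.

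**Step 1: independent tests.** The chance of at least one false positive in k tests is 1 − 0.95^k.
- k = 14: 1 − 0.488 = 51%
- k = 13: 1 − 0.513 = 49%
- k = 12: 1 − 0.540 = 46%

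**Step 2: correlated tests.** For k equally correlated two-sided z-tests with no true effect, by simulation for 14 and by numerical integration for 12:

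| ρ (assumed) | 14 tests | 12 tests |
|---|---|---|
| 0 | 51% | 46% |
| 0.3 | 44% | 40% |
| 0.5 | 35% | 32% |
| 0.7 | 25% | 23% |
| 0.8 | 20% | 19% |

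**Step 3: how many false positives.** For 14 tests the expected number is 14 × 0.05 = 0.70. Under independence:
- none: 0.95^14 = 0.488
- exactly one: 14 × 0.05 × 0.95^13 = 0.359
- two or more: 1 − 0.488 − 0.359 = 0.153, about 15%

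**Step 4: price of the bluntest correction.** Bonferroni for 14 gives 0.05/14 = 0.00357 per test, with critical value 2.914. A test with 80% power at 0.05 then has power Φ(1.960 + 0.842 − 2.914) = Φ(−0.112) = 46%. The effect detectable with 80% power rises by (2.914 + 0.842)/(1.960 + 0.842) = 1.34, from 0.484 to about 0.65 (normal approximation).

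**The case against.** **An article condenses, and multiplicity usually belongs in the analysis plan.** This is right in general, and a plan that is not shown may deal with it. The threshold sentence does not forbid adjustment either, since Holm-adjusted p-values are also compared with 0.05. A reader might infer that the trial has no error control at all, and the article does not establish that. But the article is not merely silent: it gives every construct primary status and fixes one level for all analyses. Taken at face value, those two statements form an unadjusted rule.

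**Table 1 may be only an inventory of measures.** The text introduces it as a summary of the survey's measures, and a questionnaire on adverse experiences is an unlikely intervention outcome. The bold block titles could even be read as two primary domains, which would give 1 − 0.95² = 9.75% if independent. The heading may well be loose, but no domain score is defined and the regressions are run on study outcomes. The two-domain reading therefore has no support in the text.

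**No rule says that one significant scale counts as success.** This stands. The family-wise figures are conditional on that reading, and the article offers no other success rule.

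**The scales are correlated.** This also stands. The same child answers them in one survey, and two constructs share an instrument. A reader might take 35% to 51% as the established range, but that covers only ρ from 0.5 down to 0.

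**Factor analysis and structural equation models could reduce the number of tests.** They could, but neither is named as the primary test. The regression models are described only as covariate-adjusted, and no joint test is stated.

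**Conclusion.** The point holds in a limited form. The article labels 14 distinct constructs primary, sets 0.05 for all analyses, powers one unnamed test, and states no lead outcome, composite, order or adjustment. If any significant scale is read as impact, the false-positive risk is 51% for 14 independent tests and 20% at a correlation of 0.8. With 12 tests it is 46% and 19%. The size rests on an assumed equal correlation and on the any-scale reading. The direction does not depend on the exact values: every case shown is several times 5%.

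Three stronger readings go too far:
- A reader might infer that one or two significant scales are simply what chance would produce. One would be unremarkable, but two or more occur only about 15% of the time under independence.
- A reader might add the discrete choice experiment, the parent gender measure and the structural paths to the primary family. The article does not label them primary, and they are not in these figures.
- A reader might conclude that only a single index will do. For an intervention with ten target areas, an index is one legitimate choice among several.

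**What to change.** Before endline data are analysed, choose one of two routes:

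1. **One primary outcome.** Name a single scale or a pre-defined index, tested at 0.05, and make the remaining scales secondary. This matches the single test in the sample size section.
2. **Several primary scales.** List them, and replace the significance sentence with a family-wise level of 0.05 across them, by Holm or Romano-Wolf step-down.

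Under either route, label all other analyses secondary or exploratory. In Table 1, delete the repeated Persistence row, say whether adverse life experiences is a covariate rather than an outcome, and count the shared teamwork instrument once.

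The cost is a change of wording and, for the second route, a short routine in Stata. The downside of the second route is a stricter threshold for individual scales. Plain Bonferroni for 14 would take a test from 80% to about 46% power; Holm is never less powerful than Bonferroni, and fewer primary scales also soften the loss. The downside of the first route is that an index may dilute an effect confined to one module.

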The first aim of *Discover Learning* is to provide a developmentally informed rationale for the design of the intervention and to detail the process related to the development, implementation and evaluation to enhance social emotional learning and identity development in very young adolescents. The primary research objective is to evaluate the extent to which a technology-based distance learning program can positively impact social emotional learning and identity development in very young adolescents. Our theory of change posits that if 10–14 year olds are exposed to information and material matched to the developmental window of very young adolescence, are engaged in activities that combine content and practice with their siblings/near peers, parents and community, there will be high impact improvements in outcomes for key social emotional skills and mindsets, enhanced equity in gender norms, beliefs and behaviors, and, health and well-being outcomes. These improved outcomes will help to set adolescents on early positive trajectories toward improved health, educational and economic outcomes. The results of this study will be used to: (1) determine the impact of *Discover Learning* on social emotional learning and identity development outcomes, (2) explore how technology can be used to amplify social emotional learning and identity development, and (3) examine how involvement of siblings/near peers, parents/caregivers and extended family can amplify study outcomes. *Discover Learning* is a strategic partnership between University of California Berkeley, Health for a Prosperous Nation (HPON), Camara Education and Ubongo Kids.

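### The p < 0.05 rule covers all analyses, so mediators, modifiers and SEM paths found by searching would be called significant on the same footing as the programme's main effect

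*Protocol article*

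**What the plan says.** In the protocol article, Data Analysis gives one significance rule: "Statistical significance for all analyses will be set at" p < 0.05. The rule has no exception and no adjustment. The same paragraph goes on: "Structural equation modeling (SEM) will be used to test structural paths between latent constructs", and then "Potential mediating and modifying variables will be assessed". The mediators and modifiers are not named or counted, and neither are the paths.

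Two other places show what these results are for. The end of the Introduction states a single primary research objective, the programme's impact on social emotional learning and identity development. It then lists three uses of the results, the last two being to "explore how technology can be used to amplify social emotional learning and identity development" and to "examine how involvement of siblings/near peers, parents/caregivers and extended family can amplify study outcomes". Under Baseline and Endline Survey, the survey "seeks to identify which components of the intervention hold the greatest promise for innovation, scale, and adaptation".

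The Sample section sizes the study "for a two-tailed" t-test at 0.05 with 80% power. It mentions no interaction, mediation or path effect.

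**The concern.** A protocol article may leave the list of modifiers to the analysis plan. Here, though, the article has already fixed the rule by which any such result will be judged. Read as written, that rule treats a modifier or path picked out from many candidates exactly like the effect of the programme itself.

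That matters because the results are meant to be used. If one kind of family involvement appears to strengthen one outcome at p < 0.05, the text allows it to be reported as a significant amplifier. It could then influence which components or families are favoured at scale, although it may be the one chance finding among many looks. Naming a lead outcome for the main effect would not cure this, because the modifier and path tests would still be judged at 0.05.

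**Working it through.** The article gives no figure for this error rate, so there is none to reproduce. The size has to be shown under a stated assumption about the number of tests.

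**Inputs**

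- Threshold: two-sided 0.05 per test, unadjusted (Data Analysis; the Sample section also uses a two-tailed 0.05 test).
- Candidate amplifiers: 3, namely siblings/near peers, parents/caregivers and extended family (Introduction). Testing each of them as a modifier is my assumption.
- Outcomes: Table 1, described by "A summary of all measures included in the survey are listed in Table 1", has 15 rows under a primary-outcome heading. Persistence appears twice, so there are 14 distinct constructs. That each would be crossed with each amplifier is also an assumption.
- Correlation between test statistics: not given, so shown from 0 to 0.8.

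**Formulas**

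- Independent tests, all nulls true: probability of at least one false positive = 1 − 0.95^k.
- Equal pairwise correlation ρ: 1 − E[{Φ((c − √ρ·U)/√(1−ρ)) − Φ((−c − √ρ·U)/√(1−ρ))}^k], with U standard normal and c = 1.96, by numerical integration.
- Expected false positives = 0.05k, whatever the correlation.

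**Results**

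| Case | k | ρ = 0 | ρ = 0.5 | ρ = 0.8 | Expected false positives |
|---|---|---|---|---|---|
| 3 sources, one outcome | 3 | 0.143 | 0.125 | 0.098 | 0.15 |
| 3 sources × 14 constructs | 42 | 0.884 | 0.583 | 0.284 | 2.1 |

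For example, 1 − 0.95^3 = 0.143, 1 − 0.95^42 = 0.884 and 0.05 × 42 = 2.1.

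To see where the chance passes one half with independent tests: k = 13 gives 1 − 0.95^13 = 0.487 and k = 14 gives 1 − 0.95^14 = 0.512. So at least 14 independent, truly null tests are needed, and more if the tests are correlated.

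I give no corresponding figure for the SEM paths. Counting every pair of constructs would assume that all pairs are tested and all are null. Table 1 contains closely related constructs: empathy, generosity and utu (the last measured partly with a compassion scale), and teamwork and social responsibility measured with one instrument. Many paths among these are plausibly real.

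**The case against.** The strongest reply is that this is mostly an omission. The list of modifiers, the path model and the handling of multiplicity are commonly left to an analysis plan or full protocol, neither of which is shown. Family-wise control is not normally demanded of mediator, modifier and SEM analyses. The Introduction also gives these questions softer standing: they sit apart from the single primary research objective and are worded as exploring and examining. The sentence on components describes what the survey is meant to capture and specifies no hypothesis test.

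Much of this stands. The missing list is not a finding, nor is the absence of family-wise control in itself, and the Introduction's wording does count for something. It does not remove the point, because Data Analysis positively applies p < 0.05 to everything and carries none of that softer wording over to these tests.

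A reader might also infer that a false amplifier or pathway is likely to be declared. The document does not support that. It states no number of tests, a handful of modifiers on one outcome would give a modest error rate, and even 42 tests give 0.28 at correlation 0.8. Nor does the unpowered state of these tests raise their type I error.

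**Conclusion.** The point holds as a badly worded rule. The text gives modifiers, mediators and paths found by searching the same claim to significance as the main effect, while intending to use them to say what amplifies outcomes and what to scale.

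Its size depends on a count that the article does not give. Under the assumption of three involvement sources, the chance of at least one false positive is about 0.10 to 0.14 for one outcome and about 0.28 to 0.88 for 14 constructs, over correlations from 0.8 down to 0. These figures assume that every null is true, and they fall if some effects are real. Even the smallest is about twice the nominal 0.05 (0.098/0.05 = 2.0). The point is worth correcting but does not bear on the primary objective.

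**What to change.** In Data Analysis, restrict the p < 0.05 rule to the main-effect analyses. Add that mediator, modifier and SEM path analyses are exploratory, are reported as estimates with 95% confidence intervals, and are not used as confirmatory evidence that a component or subgroup works better.

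I would not add a formal adjustment for selected interaction tests. It is not needed once the analyses are labelled exploratory. Study Design also describes only participants who receive the programme or its smartphone version, so it gives no untreated comparator against which a programme-by-modifier interaction could be tested.

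The cost is a sentence or two, with no new data or participants. The small downside is that the two amplifier questions in the Introduction would be answered as hypothesis-generating. The change does not resolve multiplicity across the Table 1 main effects, which needs its own decision.

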
## Discussion and Conclusion

This paper describes the protocol for *Discover Learning*, an intervention designed for very young adolescents to support social emotional learning and identity development using distance and technology-facilitated, experiential learning. Very young adolescence represents a population and a unique window of opportunity where investments in social emotional learning can lead to positive health trajectories and protect against a variety of health risks that emerge in later-adolescence. *Discover Learning* is unique because the intervention and evaluation design incorporated important insights from the developmental science of adolescence to enhance the effectiveness of social emotional learning during very young adolescence. Social emotional learning is not only important during early adolescence, but the mindsets and skills included in Discover Learning empower VYAs to cope with stressful life events in the proximal and distal future (70). Moreover, *Discover Learning* tests an innovative approach of delivering experiential social emotional learning through distance and technology enabled modalities in a low resource context. While other programs have been designed to include social and emotional learning to youth in low- and middle-income countries (71, 72), many of these programs are delivered in school and few include experiential activity learning that engages siblings and adults (73, 74). This study will make a novel and unique contribution to literature on strategies for delivering experiential distance-learning programs that engage siblings, parents/caregivers and extended family. Analysis from qualitative in-depth and key informant interviews will provide additional insight into the acceptability and integrity of the implementation strategy. These findings have the potential to be replicated in other low-resource contexts.

